## Abstract

**Background:**

The ability to retrieve specific memories is a cognitive and emotional protective factor. Among the most effective techniques to generate autobiographical memories is the use of audio-visual stimuli, particularly images. Developing and improving techniques that facilitate the generation of such memories could be highly effective in the prevention of depressive symptoms, especially in the elderly population. The aim of the present study is to examine how the level of personal relevance of pictures as autobiographical memory cues to induce positive emotions may affect an individual’s emotion regulation.

**Methods:**

The participants, 120 older adults aged 65 and over and 120 young adults aged between 18 and 35, of both sexes and without depressive symptoms, will be induced to a negative mood state by means of viewing a film clip. Following the negative mood induction, the participants will be shown positive images according to experimental group to which they were randomly assigned (high personal relevance: personal autobiographical photographs; medium personal relevance: pictures of favourite locations associated with specific positive autobiographical memories; and low personal relevance: positive images from the International Affective Picture System). We will analyse the differences in subjective (responses to questionnaires) and objectives measures (EEG signal, heart rate variability and electrodermal activity) between the groups before and after the induction of negative affect and following the recall of positive memories.

**Discussion:**

The use of images associated with specific positive autobiographical memories may be an effective input for inducing positive mood states, which has potentially important implications for their use as a cognitive behavioural technique to treat emotional disorders, such as depression, which are highly prevalent among older adults.

**Trial registration:**

ClinicalTrials.gov NCT04251104. Registered on 30 January 2020.

## Administrative information

Note: the numbers in curly brackets in this protocol refer to SPIRIT checklist item numbers. The order of the items has been modified to group similar items (see http://www.equator-network.org/reporting-guidelines/spirit-2013-statement-defining-standard-protocol-items-for-clinical-trials/).

## Introduction

### Background and rationale {6a}

The probability of suffering from depression at some point in one’s life is superior to that of other mental disorders, such as anxiety, for example [1]. Its prevalence is elevated, and it is estimated that between 10 and 20% of the population will develop a depressive disorder during their lives [2]. Depression can thus be considered one of the most common health disorders, especially in older adults, given that clinically significant depressive symptoms are present in 15% of community-dwelling older adults [3] and in 46.5% of institutionalized older persons [4]. Depressive symptoms in older adults may be the result of multiple changes occurring in this life period (e.g. loss of loved ones, worsening health, social isolation, reduced independence, etc.). A number of authors have suggested that when older adults are unable to cope with and adapt to these new circumstances, depressive disorders may appear [5]. Furthermore, depressive symptomatology in older people is associated with a higher risk of morbidity, self-neglect, suicide, impaired physical, social and cognitive functioning, decreased quality of life and even a higher risk of mortality [3, 6, 7]. Consequently, preventing and mitigating depressive symptoms should be a core element in improving mental health and quality of life in healthy older adults. For this reason, studies should not be directed solely towards the development and improvement of treatments for clinical depression, but also towards studying variables that can help prevent the appearance of depressive symptoms and/or reduce the presence of non-clinical depressive symptoms in healthy ageing.

#### Emotion regulation in ageing and depressive symptomatology

Depressive symptomatology represents a significant shift away from the affective balance within which a person moves, and as such, they are related to problems or difficulties in emotion regulation. Hence, successful emotion regulation may increase positive affect and diminish negative affect [8].

How individuals manage emotions, be they positive or negative, changes as we grow older, and it has been suggested that, despite the impairment of cognitive functioning in ageing, emotion regulation may improve with age [9]. In the same line, studies have reported a change in priorities with age, with older adults tending to focus on positive emotional goals, distancing themselves from negative information or mood states, generating, in turn, a positivity effect, whereby the recall of positive information increases significantly [10], and negative situations are avoided [11]. An example of this positivity effect is found in autobiographical memory recall, where the number of positive memories retrieved tends to increase with age [12], since, when recalling past events, older adults typically remember them more positively compared to young adults [13, 14]. Nonetheless, some studies have suggested an opposite effect, where the use of emotion regulation strategies reduces with age [15]. Finally, some authors have even posited that emotion regulation is unaffected by ageing [16, 17].

#### Autobiographical memory for positive mood induction

Over the years, different effective emotion regulation techniques have emerged, with one of the most significant being the use of autobiographical memories. These techniques are based on the idea that individuals are able to regulate negative emotional mood states using personal episodic information stored in memory [18]. Various studies have demonstrated that training access to specific positive events (referring to something with positive emotional content that occurred at a concrete moment in a specific space and time, lasting from seconds to hours) is effective in regulating emotions and improving mood state in older adults, reducing negative mood and increasing positive emotions [19]. Taking these results into account, cognitive interventions aimed at increasing specific positive autobiographical memories (e.g. life review [20] or memory specificity training (MEST) [21]) have been developed. These therapies have been shown to be a successful method of reducing depression through improving autobiographical memory specificity [22]. This mood improvement is even possible after the induction of a negative mood state [23, 24]. Additionally, a number of studies have also reported that the ability to retrieve specific autobiographical memories is an indicator of emotional well-being [25] and is correlated with enhanced life satisfaction [26].

One of the key types of autobiographical memories is self-defining memories. Characterized by the vividness and intensity of their affective tone and related to self-discovery, self-understanding and self-images, these memories help us to create and understand our life story [27]. Integrating such memories to enrich our self-understanding is a predictor of more successful emotion regulation [28]. In older adults, self-defining memories are associated with personal maturity, emotion regulation and the creation of meaning [29]. Compared with younger adults, older people’s self-defining memories present greater levels of vividness, importance and positive affect, especially with regard to significant relationships, achievements, bringing up children, etc., although their specificity is lower compared to younger adults’ memories [29].

Autobiographical memories have been used as a procedure for inducing different mood states, being especially effective in the induction of positive mood states [30, 31]. These procedures based on autobiographical memory recall require participants to generate the emotion they felt when they experienced a specific personal event, recalling it as vividly as possible and re-experiencing sensations, emotions, perceptions and reactions [32]. El-Ziab posits that the more accessible and meaningful the autobiographical memories are for the participant, the more effective these procedures are in regulating negative mood [33].

#### Importance of the use of images in mood induction

As suggested by Holmes and Mathews [34], negative mood state is typically accompanied by distressing mental images. In this sense, several studies have shown that imaging positive events enhances mood more than verbal processing [35, 36]. These findings have motivated the development of techniques based on visual stimuli to reduce these types of symptoms and generate positive emotions [37]. According to Sitaram et al. [38], pictures have proven to be one of the most effective cues for capturing the complexity of an emotional recall scenario. Their effectiveness might lie in the fact that, compared to other types of stimuli, images have a direct correspondence to sensory experience and are thus more real [39], so helping a person to access emotions related to their autobiographical memories [40].

Given the importance of autobiographical memory and images when inducing positive mood states, it seems necessary to determine what types of pictures might be more effective in eliciting mood states through the retrieval of memories related to specific positive events. A number of studies have reported that viewing standardized images, such as those taken from the International Affective Picture System (IAPS) [41], can activate motives, albeit less strongly than life’s real transactions, given that the personal relevance or ecological validity for the participant of such images may be low [42]. This finding suggests hypotheses related to the possibility that images with greater personal relevance for a participant, that is, an individual’s own photos, might significantly increase the induction of a positive emotional state.

#### Objective measurement of emotional response: physiological correlates

Among the methods most widely used to objectively assess emotional response are brain activity measurement (e*lectroencephalogram*) and *physiological measures*, such as *electrodermal activity* and *heart rate*.

##### Measurement of brain activity

Emotions generate temporal patterns of brain activation [43], which can be identified and discriminated using the *electroencephalogram* (EEG) [44, 45].

The use of the EEG signal has facilitated the study of the neurophysiological correlates through the amplitude and frequency changes generated in response to different stimuli (e.g. picture viewing) [46], enabling different emotional states to be distinguished. A number of studies have reported that low frequency bands are associated with emotional processing [47, 48] and, alpha bands, specifically, are related to positive emotions [49]. On the other hand, high frequencies (gamma bands) are relevant to cognitive processes that include feelings and emotions [50]. According to Li and Lu [51], these bands are especially significant for the classification of emotions using images as stimuli.

Other studies have shown that the left and right frontal regions are associated with positive and negative emotional responses, respectively [52]. In the same line, research has mainly focused on analysing alpha band asymmetries in the frontal cortex to understand the hemispheric specialization of emotions [53]. Findings suggest that, compared with negative emotions, positive emotions present higher frontal coherence as regards the alpha and beta bands in the right superior parietal lobe [54]. Other studies have reported decreased alpha and theta power in the left frontal region in response to positive processing, and a decrease in the same bands in the right frontal region triggered by negative processing, which suggests band power is associated with the valence of the stimulus [55].

Marosi et al. [56] found that higher delta frequencies in left and right frontal, parietal and temporal regions and high beta frequencies in the left fronto-temporal and temporal regions are associated with joy. In addition, higher delta and alpha frequencies appear in response to exposure to pleasant images [46]. These findings corroborate previous studies finding greater alpha band activity in the left frontal region during positive emotion processing [57]. Moreover, it has been shown that high arousal stimuli generate a decline in alpha power [58] and increased delta and theta power [53, 59]. Studies have also revealed that positive stimuli, such as pleasant odours, happy musical excerpts and pleasant TV commercials, may induce significantly lower frontal alpha power and higher theta power in the left hemisphere [60–62]. Strong synchronization has been found between theta and delta waves in response to emotional stimuli [48], which suggests that synchronization between these two brain waves during autobiographical memory tasks may be considered a marker of emotional arousal [63].

Autobiographical memory has been associated with a network of predominantly lateralized brain regions, and thus, mood induction procedures using autobiographical memory tasks generate bilateral activation [64]. Specifically, a pattern of left lateralization during the initial search for general autobiographical knowledge has been found, while the subsequent re-experiencing of the memory has been associated with the right hemisphere, especially the posterior cortical regions [65], also preferentially associated with emotional processing and social cognitive processes [66, 67].

##### Autonomic nervous system

As previously mentioned, emotions involve psychophysiological processes, and thus generate changes in variables such as heart rate and blood pressure [68] or galvanic skin response [69].

A number of studies have reported higher heart rate variability (HRV) in older adults as self-reported positive emotion and well-being increase [70], with high HRV being associated with greater emotional well-being and better emotion regulation [71–73]. Then, the health benefits of positive emotions on health may derive from reduced cardiovascular activation associated with decreased sympathetic nervous system (SNS) activation and an increase in activation of the parasympathetic nervous system (PNS) [74]. Furthermore, positive emotions facilitate cardiovascular recovery following negative emotions [75]. Low heart rate has been associated with pleasant or relaxed emotional states, while heart rate accelerations occur in response to intense emotional states, sexual arousal or mental effort [76].

Furthermore, electrodermal activity (EDA), or galvanic skin response (GSR), has been associated with SNS activity [77, 78]. Studies such as that by Codispoti et al. reported higher skin conductance response to exposure to emotional pictures [79]. The use of EDA is highly effective in measuring the level of an individual’s emotional arousal, regardless of the emotional valence of the stimuli, since it is able to quantify changes in the SNS [80]. Various studies have identified changes in EDA (increase in peaks) following exposure to images taken from the IAPS [81].

## Objectives {7}

The ability to retrieve specific memories is a cognitive and emotional protective factor. Thus, developing and improving techniques that facilitate the generation of such memories, which are able to enhance mood state, could be highly effective in the prevention and/or reduction of depressive symptoms in healthy older adults. Consequently, the aim of the present study is to delve deeper into the knowledge and effectiveness of different visual stimuli in inducing positive emotions and reducing negative emotions, examining how the level of personal relevance of pictures as autobiographical memory cues may affect an individual’s emotion regulation. Importantly, this new knowledge could also be used in interventions focused on the training of specific positive memories with the aim of improving its efficacy in the treatment of clinical depression in the elderly population.

Additionally, given the differences in emotion regulation between young and older adults, we aim to assess whether the influence on emotion regulation of the level of personal relevance of the images differs according to a person’s age.

The main aim of this study, then, is to experimentally evaluate how the level of personal relevance of the images used as stimuli to access specific positive autobiographical memories can improve emotion regulation, especially in older adults. From this primary aim, we derive the following specific objectives:
To experimentally study the impact of the personal relevance of pictures on the improvement of mood state, following negative mood induction. To this end, we will use three types of images, classified according to their personal relevance: (a) personal autobiographical photographs (high personal relevance), (b) images of locations related to the participants’ lives (medium personal relevance) and (c) images from the IAPS (low personal relevance).Additionally, as suggested by Talarico et al. [82], events remembered with a high sense of reliving induce stronger emotions. For this reason, we will also examine the degree of reliving in the autobiographical memories evoked by the three types of images.To analyse any age-related differences in the effectiveness of the use of the three types of images to regulate emotion. We will compare the efficacy of the three categories of pictures (high, medium and low relevance) in inducing positive mood states in a group of young adults and a group of older adults.

The objective measures of emotion (EEG, EDA and HRV) will be used to substantiate the effects of emotion induction mechanisms observed in self-evaluations.

## Trial design {8}

This is an exploratory randomized controlled study designed to compare the effectiveness of three types of autobiographical stimuli, classified according to their level of personal relevance, in the induction of positive emotions resulting from the retrieval of specific positive autobiographical memories. The study sample will comprise a group of adults aged 65 years and over and a group of young adults aged between 18 and 35. Each participant will be randomly assigned to one of three parallel groups (high, medium and low personal relevance images). The allocation ratio will be 1:1:1.

## Methods: participants, interventions and outcomes

### Study setting {9}

The study sample will comprise a group of healthy adults aged 65 years or over and a group of healthy young adults aged between 18 and 35. The first group will consist of adults aged 65 years or over, recruited in the city of Albacete (Spain) from senior citizens’ associations and centres, from a cultural association for older people (Alumni Association of the University of Experience [*Asociación de Alumnos de la Universidad de la Experiencia*, ALUEX]), from the José Saramago University Programme for older adults and from different socio-cultural centres. The second group will comprise young adults, aged between 18 and 35 years, who will be recruited from among students and workers at the University of Castilla-La Mancha (Albacete Campus), Spain.

The study will include both men and women, aiming for a proportion of at least 40% and 60%.

#### Eligibility criteria {10}

All participants interested in the study will be asked to complete preliminary questionnaires to assess their eligibility before being assigned to the experimental groups.

Participation will be dependent on the following inclusion criteria:
Older adults will present no symptoms of cognitive impairment. The self-administered Test Your Memory (TYM) will be used to assess cognitive performance [83, 84].Absence of depressive symptomatology, which will be assessed using the Patient-Reported Outcomes Measurement Information System-Depression [85].Given the high comorbidity between anxiety and depression [86, 87], it was decided that both young and older participants should present no symptoms of anxiety. This will be assessed using the Patient-Reported Outcomes Measurement Information System-Anxiety [85].No sensory deficits that might impact performance in the experiment and the psychological tests.Sufficient literacy skills to understand the instructions for the experiment and the psychological tests.Signed informed consent.

#### Who will take informed consent? {26a}

Two trained research psychologists will present the trial to possible participants. Participants will then receive information sheets and any questions about the study will be resolved. Finally, research psychologists will obtain written consent from those willing to participate in the trial.

#### Additional consent provisions for collection and use of participant data and biological specimens {26b}

Not applicable. Participant data will not be used for purposes that are separate from the main trial.

### Interventions

#### Explanation for the choice of comparators {6b}

The conditions of medium and high personal relevant images will be compared with IAPS images (low personal relevant condition). IAPS [41] is traditionally considered a valid system for affectively eliciting stimuli that can be used as a representative tool, for example, in mood and emotion induction studies. For this reason, its selection as comparator is justified.

#### Intervention description {11a}

##### Screening phase

The first screening phase will be conducted with all the potential participants, both young and older adults. The screening phase will take place in different sessions in the different recruitment centres until the minimum necessary number of participants is achieved. The sessions will be conducted in both group and individual formats. The instruments described in the corresponding section will be administered and individuals not meeting the inclusion criteria will be excluded from the study.

##### Pre-experimental phase

The participants from both groups (older adults and young adults) will be randomly assigned to one of the three experimental groups, the condition of which will differ according to the type of stimulus used to elicit specific positive autobiographical memories: (1) low personal relevance condition: positive images taken from the International Affective Picture System [41]; (2) medium personal relevance condition: pictures of places related to the participants’ lives (the most important or characteristic places in their town or city, or a place they have visited, etc.); and (3) high personal relevance condition: participants’ own photographs related to their positive autobiographical experiences (see Fig. 1).

**Fig. 1 Fig1:**
[figure not shown]
Randomization phase

We will thus have three types of images varying in their level of personal relevance for each participant. The first type of images is pictures taken for the standardized IAPS. There will be a total of 40 pictures selected by the research team according to their level of positive valence (emotional valence values between 7.03 and 8.34). The participants will be asked to choose the 6 photos that best enable them to generate a specific positive autobiographical memory.

The second type of images used will be photos of locations and places that are significant for the participant, which will be selected following a prior interview in which the participant will be asked to name places that evoke specific positive autobiographical memories. These images will be taken from the Internet. We will select various images of each location, giving participants the opportunity to choose the one which best fits their memory.

The third type of images will be autobiographical photographs selected by participants from their own collection. Participants will be asked to previously select six photos, for which they can recall the exact moment they were taken and which are related to events that have made them feel happy during their lives. These six events will be those they are asked to recall in the experimental task.

For each of the memories retrieved in the three conditions, the following factors will be assessed: (1) the degree of nostalgia generated by the memory; (2) the intensity of the positive emotion evoked by the memory; (3) whether the participant was a spectator in the event (“as if I were watching a film”) or an actor (“as if I were seeing it with my own eyes or recording it”); (4) the significance of the event in the person’s life; (5) personal growth since the event occurred; (6) belief that the event has led them to better understand themselves and what life means; and (7) belief that they have learnt more about what life means as a result of the event.

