### Participant timeline {13}

Participant recruitment is expected to begin in October 2020 and continue for 2 months. Nevertheless, if the minimum number of participants in each experimental group is not reached in early December, the recruitment period will be extended until the required minimum is reached. In this phase, those who agree to participate will complete the screening questionnaires.

The pre-experimental and experimental phases will take place 7–21 days after randomization. Both phases will take place on the same day. In the pre-experimental phase, participants will select the images to be displayed in the experimental task according to the group to which they are assigned (low, medium or high personal relevance). Finally, in the experimental phase, they will complete the mood questionnaires and the experimental task.

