#### Implementation {16c}

All patients who give consent for participation and meet the inclusion criteria will be randomized.

The random assignment of participants will be conducted by a member of the Psychology Department blinded to the objectives of the study. This staff member will send a third research psychologist a list with the random assignation of each participant to each intervention group. This psychologist will not be involved in the recruitment of participants or in assessing the outcomes of the study. The psychologists responsible for participant recruitment will not be allowed to receive information about group allocation.

Throughout the study, the randomization will be conducted by the same member of the Psychology Department in order to keep the data management and the statistician blind to the study condition. Thus, randomization will be conducted without any influence from the researchers involved in the study.

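### No entry criterion asks whether a candidate could supply the images for every arm, so participants unable to do so may be lost after allocation, plausibly most often from the high-relevance arm

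*Protocol article*

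**What the plan says.** The Protocol article's Eligibility criteria {10} opens its list with the statement "Participation will be dependent on the following inclusion criteria". The list covers cognition (older adults), depressive symptoms, anxiety, sensory deficits, literacy and consent. Photographs and places are not mentioned. Implementation {16c} then states: "All patients who give consent for participation and meet the inclusion criteria will be randomized".

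Image selection follows allocation. Participant timeline {13} says: "The pre-experimental and experimental phases will take place 7–21 days after randomization". In the first of these phases, "participants will select the images to be displayed in the experimental task according to the group to which they are assigned". The schedule table shows the same order.

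The text after Fig. 1, under Intervention description {11a}, sets a different task for each arm:

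- **High relevance:** "Participants will be asked to previously select six photos, for which they can recall the exact moment they were taken". The photographs come from the participant's own collection and must relate to happy events.
- **Medium relevance:** in an interview, "the participant will be asked to name places that evoke specific positive autobiographical memories". The team then finds the images on the Internet. No number of places is given.
- **Low relevance:** the team supplies 40 pictures. "The participants will be asked to choose the 6 photos that best enable them to generate a specific positive autobiographical memory".

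Every participant views six pictures (Experimental phase). Criteria for discontinuing or modifying allocated interventions {11b} removes anyone who does not finish the whole trial. Recruitment {15} continues until each group has its minimum number.

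**The concern.** Only the high-relevance arm depends on material that the participant must already own. A person without six suitable photographs is eligible and can be randomised to any arm. In the low arm the lack never comes to light. In the high arm it comes to light after allocation, and one of two things can follow.

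If the person cannot finish, the exclusion rule removes them, and continued recruitment may replace them with someone who can comply. The high arm is then selected on a characteristic that was not applied in the same way to the other arms. That characteristic is plausibly related to outcome on the protocol's own reasoning: Objectives {7} calls the ability to retrieve specific memories a protective factor, and the Background links it to emotional well-being. The high-versus-low contrast would then mix the effect of the pictures with the effect of selection. The Background also reports that older people's self-defining memories are less specific than those of younger adults, so the loss may differ by age and reach the age comparison, a stated objective.

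If the person is instead tested with photographs that do not meet the description, nobody is lost, but the high-relevance condition is delivered in weaker form.

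**Working it through.** **Does the plan prevent the problem or correct it later?**

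1. Entry: no criterion on image material, and all who meet the criteria are randomised.
2. Order: images are selected after allocation and for the assigned arm only, so inability is observed in one arm at a time.
3. Removal: non-completers are excluded, and recruitment runs until the groups are full.
4. Adjustment: the covariate rule in Statistical methods {20a} tests the PROMIS and PANAS scores and immersion in the film clip. None of these measures possession or recall of suitable material.
5. Imputation: the approach in {20c} is aimed essentially at unanswered screening items.

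Nothing in this chain prevents or repairs loss that depends on the arm.

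**How large could it be?** The plan gives no rate of inability, so there is no planned figure to reproduce. What follows is illustration.

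From the plan: 40 participants per condition in each age group (Sequence generation {16a}), so 80 per arm and 240 in all.

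Assumed:
- a share q = 5%, 10% or 20% of the high arm cannot comply and is excluded, with no such loss in the low arm;
- those lost are the lowest q on a normally distributed trait;
- the trait correlates r = 0.2 or 0.5 with the outcome, which has unit SD.

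Expected losses per age group in the high arm: 40 × 0.05 = 2, 40 × 0.10 = 4, 40 × 0.20 = 8. Over both ages the high arm keeps 76, 72 or 64 of 80, and the trial keeps 236, 232 or 224 of 240.

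Bias of high versus low, in SD = r × φ(z_q) / (1 − q), where z_q is the q-quantile of the standard normal. The factor φ(z_q)/(1 − q) is 0.109, 0.195 and 0.350.

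Type I error of a two-sided 5% comparison = Φ(−1.96 + b/SE) + Φ(−1.96 − b/SE), where b is the bias, n_high is the number kept in the high arm, and SE = √(1/n_high + 1/80).

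| q | n_high | SE | Bias, r = 0.2 | Type I error | Bias, r = 0.5 | Type I error |
|---|---|---|---|---|---|---|
| 5% | 76 | 0.160 | 0.02 SD | 5.2% | 0.05 SD | 6.3% |
| 10% | 72 | 0.162 | 0.04 SD | 5.7% | 0.10 SD | 9.2% |
| 20% | 64 | 0.168 | 0.07 SD | 7.0% | 0.18 SD | 18.1% |

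The bias depends on q and r, not on the number tested, so replacing those lost does not remove it.

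**Age comparison.** If q were 5% in one age group and 20% in the other, with r = 0.5 in both, the arm contrast would differ between ages by 0.175 − 0.054 = 0.12 SD with no true difference.

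If ability to comply with every arm were checked in all candidates before allocation, the bias from this source would be zero in this illustration.

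**The case against.** The strongest reply is that the problem may hardly arise. Participants are screened for depression and anxiety, and older adults for cognition. They come from associations, cultural centres and a university, and they have 7 to 21 days before the session. Six happy photographs may be a low bar for them. Candidates also receive an information sheet and a verbal explanation before consent, so some who could not comply may decline at that stage. This stands as a reason to expect a low rate. It does not establish one: the sheet is not shown, and the protocol gives no figure. The illustration is also severe, since it assumes that those lost are exactly the lowest on the trait.

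Three stronger readings are tempting, and the document does not support them.

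- *The arms hold different populations.* Allocation is random within age group. The arms diverge only if some people cannot comply, are removed, and differ in prognosis. The document shows the route, not that this will happen.
- *The filter acts in the high arm only.* The medium arm must name places tied to specific positive memories, and the low arm must pick pictures that cue such memories. The high arm's demand is plausibly the heaviest, because it alone needs owned material, but no rates by arm are given.
- *Inability always favours the high arm.* This follows only if the person is removed. Testing with unsuitable photographs would tend to shrink the contrast.

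A reader might also say that a condensed article leaves such checks to the full protocol. But the article lists the criteria on which participation depends and says that all who meet them are randomised. The point rests on what is stated.

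Finally, having every candidate pick out photographs and places at screening would take time (the schedule allows 25 minutes for one arm's selection) and could rehearse high-arm memories in low-arm participants. That is a fair objection to a full selection exercise, but not to a yes/no question.

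**Conclusion.** The concern holds as a risk. The entry criteria, the order of allocation and image selection, the unequal demands of the arms, the exclusion of non-completers and recruitment to a full group together allow loss after randomisation that depends on the arm. Neither the covariate rule nor the imputation plan addresses it.

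Its size is unknown. Under the assumed 5% to 20% inability and correlations of 0.2 to 0.5, the bias in high versus low is about 0.02 to 0.18 SD, with type I error between 5.2% and 18.1%. At 5% inability it is small (at most about 0.05 SD). It becomes material only when many cannot comply and the trait is strongly related to outcome. The change is worth making because it is cheap and removes this source of bias by design. Re-analysis cannot give suitable photographs to someone who never had them.

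**What to change.** Add one inclusion criterion to Eligibility criteria {10}, checked before randomisation: the candidate has, and could bring, six own photographs that meet the description given for the high-relevance arm, and could name enough places linked to specific positive memories to supply six pictures. The number of places is inferred from the six pictures viewed in the experimental phase, so the protocol should state it.

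Check it with a brief yes/no question at the existing screening session, worded identically for all candidates in both age groups, without selecting or discussing any image. Report how many candidates fail it in each age group, and report by arm any randomised participant later lost for lack of images.

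The cost is one line of eligibility text and one question. The downsides are a slightly narrower population, to be stated when generalising, and a short prompt about positive memories that is the same in all arms.
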